#### Secondary objectives

The treatment groups will be compared for efficacy (success rates in second and third treatments, achievement of the planned weight loss and UF volume) and safety using the Mantel-Haenszel test stratified on center or logistic regression as appropriate.

#### Patient populations

The full analysis set will consist of all patients who received at least one treatment and had one efficacy assessment. Since the primary criterion is the success of the first treatment, no dropout is expected, and intention-to-treat and per-protocol populations will be identical except in case of deviations (for example not allowed medication or inappropriate hemodialysis modality with regard to the randomization arm).

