**Figure 2 F2:**
[figure not shown]
Visual clotting scale.

The first heparin-free dialysis treatment will be considered successful when there is: no complete occlusion of air traps or dialyzer rendering dialysis impossible (grade 4); no additional saline flushes to prevent clotting; no change of dialyzer or blood lines because of clotting; and no premature termination (early rinse-back) because of clotting.

This evaluation (clotting scoring) will be performed hourly by two independent observers. Depending on the organization at each study site, the evaluation can be performed by two nurses (the nurse in charge of the patient and a second nurse not in charge of the patient) or by the nurse in charge of the patient and a co-investigator. In case of discordance between the two observers or in the eventuality of premature session termination (grade 4), the final decision will be made by a third authorized and trained person (the principal investigator or registered co-investigators).

At each site and prior to the enrolment of patients, an organization will be implemented, and the investigator and all those involved in the study will be trained and certified with regard to scoring.

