### Justification of sample size

The main criterion of efficacy is the success rate in the Evodial group (test) compared to standard care (on-line predilution or saline flushes). After completion of the study, the analysis will follow a two-step procedure and the probability that the efficiency of Evodial is inferior to that of the standard care will be tested first. If that probability is rejected at the 5% significance level, that is if non-inferiority is demonstrated, then superiority will be tested. The probability of simultaneously falsely accepting inferiority and superiority being mutually exclusive, no adjustment of alpha error rate will be requested. According to the results, the conclusion will be: Evodial is inferior, not inferior but not superior, or superior to the standard care.

According to the data published on heparin-free treatment (with saline flushes or on-line predilution), the success rate of hemodialysis ranges from 65% to 85%. Recent works presented at the French Society of Nephrology, September 2010, meeting in Brussels, showed a 15% to 20% improvement of these success rates using preheparinated dialysis membranes (HeprAN, Gambro, or AN69 ST) [27,28]. The non-inferiority as well as superiority margins will be set to the same value of 15%. In the hypothesis of a 65% success rate (the most patient-consuming) in the control arm, a sample size of 126 patients per arm (252 for the entire sample) will provide the trial with 80% power to first conclude to non-inferiority then to superiority, with a one-tailed 5% error rate. Assuming an equal inclusion rate in all centers, 26 patients will be enrolled in each of the 10 centers, with 13 patients in each arm. Withdrawn patients will be replaced only if the patient has been randomized and no dialysis treatment could have been performed.

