#### Primary objective

The success of hemodialysis is defined as the proportion of first treatment achieved without prematurely halting dialysis or having to change blood lines or dialyzer, owing to clotting or any additional saline flush because of clotting. The 95% one-tailed confidence interval of the test-reference difference will be constructed using the Wilson method [29], and non-inferiority then superiority accepted if its lower boundary is found to be greater than −15% then +15%. The consistency of responses across centers will be confirmed using the Breslow-Day test for homogeneity of odds ratios or logistic regression as appropriate. Though unexpected, the impact of maneuvers in the control arm (predilution or saline flushes, centre-specific) will be tested and, if necessary, taken into account as a nested factor in the analyses.

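### The primary success definition does not count an off-arm anti-clotting manoeuvre or a disallowed anticoagulant as failure, so a first session kept open that way reads as a success and can distort the non-inferiority test in either direction

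*Protocol article*

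**What the plan says.** The Primary endpoints section lists four conditions for success of the first session: no grade 4 occlusion, no extra saline flush to prevent clotting, no dialyzer or line change for clotting, and "no premature termination (early rinse-back) because of clotting". The Abstract gives the same list. The Primary objective paragraph under Efficacy analysis repeats it without the grade 4 item.

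None of the three mentions an anticoagulant or an anti-clotting procedure that does not belong to the allocated arm. Yet the Background states the hypothesis that Evodial treatment can be done without flushes and without predilution, and Study design rules out switching between arms.

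Under Patient populations, "The full analysis set will consist of all patients who received at least one treatment and had one efficacy assessment". The intention-to-treat and per-protocol sets are expected to coincide except for deviations, "for example not allowed medication or inappropriate hemodialysis modality with regard to the randomization arm".

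The decision rule is a one-sided 95% Wilson interval, with "non-inferiority then superiority accepted if its lower boundary is found to be greater than −15% then +15" percent.

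**The concern.** The list treats like manoeuvres differently. If an Evodial circuit starts to clot and staff flush it with saline, the session fails. If they add predilution, or give a disallowed anticoagulant, and the circuit then stays open, every listed condition is met. That session did not show what the hypothesis claims for Evodial.

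Neither analysis set repairs this. The full analysis set keeps the session as a success. A per-protocol set removes it, although it was probably heading for failure, so the remaining sessions look better than they should.

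The gap is not symmetric between arms for changes of modality. Moving a clotting control session to Evodial needs a new dialyzer, which already counts as failure, and flushing a predilution control is already a failure. Adding predilution to an Evodial session, or to a saline-flush control, is not scored. Anticoagulant use could occur in either arm. At stake is the error rate of the non-inferiority claim, which is the first gate of the trial.

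**Working it through.** **Inputs from the article.** Justification of sample size gives "In the hypothesis of a 65% success rate (the most patient-consuming) in the control arm"; "The non-inferiority as well as superiority margins will be set to the same value of 15" percent; "a sample size of 126 patients per arm (252 for the entire sample"; and "80% power to first conclude to non-inferiority then to superiority, with a one-tailed 5% error rate". The Evodial rate under the planning hypothesis is not stated and is taken as 65%.

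**The plan's own figure.** n per arm = 2 × 0.65 × 0.35 × (1.645 + 0.842)² / 0.15² = 125.03, rounded up to 126. The stated size reproduces, and this point does not affect it. Exact binomial enumeration of the Wilson-based (Newcombe) one-sided 95% lower bound at 126 per arm gives 80.8% power at 65% versus 65%.

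**Masking model (assumed).** Take the truth at the margin: Evodial 0.50, control 0.65. Let r_E and r_C be the shares of failing sessions that are kept open by an unscored manoeuvre and counted as successes.

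- Apparent Evodial rate = 0.50 + 0.50 r_E
- Apparent control rate = 0.65 + 0.35 r_C
- Apparent difference = −0.15 + 0.50 r_E − 0.35 r_C

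The deficit shrinks when r_C < (0.50/0.35) r_E = 1.43 r_E, and grows when r_C exceeds that.

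**Probability that the lower bound exceeds −15%**, by the same enumeration:

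| Masked share of failures | Both arms | Evodial only | Control only |
|---|---|---|---|
| 0% | 5.5% | 5.5% | 5.5% |
| 5% | 6.9% | 11.7% | 3.0% |
| 10% | 8.5% | 21.5% | 1.5% |
| 20% | 12.9% | 51.1% | 0.3% |

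In the 10% row the apparent rates are 55% versus 68.5% (both arms, −13.5 points), 55% versus 65% (Evodial only, −10 points) and 50% versus 68.5% (control only, −18.5 points). In sessions, 10% of failures is 0.10 × 0.50 × 126 = 6.3 with Evodial and 0.10 × 0.35 × 126 = 4.4 with control.

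**Per-protocol deletion.** With 10% of Evodial failures masked and those sessions removed, the Evodial rate is 0.50 / (1 − 0.05) = 52.6%. Against 65% the deficit is 12.4 points instead of 15, so deletion reduces the distortion but does not remove it.

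**The case against.** The strongest reply is that the success of these sessions is inferred from silence. The endpoint concerns a heparin-free treatment, and a session given systemic heparin is arguably no longer one. Patients are enrolled because a nephrologist prescribed heparin-free dialysis, often for bleeding risk, so heparin during the session would defeat the prescription. The obvious response to clotting, a saline flush, is already a failure. This makes anticoagulant use unlikely to be common and leaves its size unknown. It does not cover added predilution, which is heparin-free, and the article itself foresees both kinds of deviation.

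Three stronger readings are tempting and are not supported.

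- A reader might infer that the definition always favours non-inferiority. It does not: masking mainly in the control arm makes a false claim less likely, and the article gives no frequencies by arm.
- A reader might infer that the test has no analysis population. The article defines a full analysis set and mentions the two others. Assigning one to each test is content that the full protocol or the SAP, neither of which is shown, commonly carries.
- A reader might object that sessions stopped early for reasons other than clotting are not failures. That is a legitimate scope choice for a clotting endpoint. Counting them all as failures would dilute the contrast equally: with 10% such stops in both arms, 0.90 × 50% = 45% versus 0.90 × 65% = 58.5%, again −13.5 points, with false non-inferiority of about 9%.

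Open-label assessment is acknowledged in the Discussion and mitigated by two observers, third-person adjudication and certified training. Those measures govern how the listed items are judged. They do not add the missing one.

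**Conclusion.** The point holds as a gap in a closed list. By its wording, the primary endpoint credits sessions that were kept open by means outside the randomised arm, and the foreseen deviations are handled only through the choice of analysis set. The bias can run towards or against non-inferiority, with the turning point at the margin where the control share is about 1.43 times the Evodial share. With 10% of failures masked, false non-inferiority is 8.5% (both arms), 21.5% (Evodial only) or 1.5% (control only), against 5.5% with none. These figures rest on assumed masking shares and a true 50% versus 65%. If such sessions are rare, the effect is small. The sample size stands.

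**What to change.** In the primary analysis, score as not successful any first session in which a systemic anticoagulant, or an anti-clotting procedure not belonging to the randomised arm, was used. Report the per-protocol set as a supporting non-inferiority analysis, not as the cure, because it deletes these sessions. Fix the rule before the blind review of data mentioned under Baseline comparability.

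The cost is a sentence of endpoint wording. No new patients are needed, which matters because Trial status reports 245 already recruited, and the deviations must be identified for the per-protocol set anyway. The rule changes how sessions are scored, not how patients are treated. The downside is slightly lower success rates, since some sessions so scored might have succeeded without the manoeuvre.

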### Study organization (in the Additional file 1 the steering committee, DSMB and HepZero investigators are listed)

#### Steering committee

In conjunction with the sponsor, a steering committee will oversee the trial. The steering committee is the main policy and decision-making committee of the study and has final responsibility for scientific conduct. The specific tasks of the steering committee are to: approve by signing the study protocol and protocol amendments; provide recommendations to solve problems in cooperation with the clinical study manager; and approve study reports and articles for publications (including abstracts) and presentation of clinical data of any investigator.

The steering committee is comprised of three investigators participating in this study, one methodologist and nephrologist (PR) and two representatives from the study sponsor, Gambro.

An independent Data and Safety Monitoring Board (DSMB) will monitor the safety and efficacy of the trial and periodically assess whether the trial should continue to the planned termination. Based on the safety data, the DSMB may recommend modifications to the protocol (for example amendments, termination of the study) and, when needed, the DSMB will decide on stopping rules. The DSMB will consist of three members. No member of the DSMB will act as an investigator for the study. Members of this board are not affiliated with Gambro, the principal investigators or the clinical investigation. They will declare any conflicts of interest if such should arise. The DSMB will report to the chairman of the steering committee, who in turn is responsible for implementing a decision to terminate the trial prematurely if deemed necessary.

## Discussion

Anticoagulation for chronic dialysis patients with contraindications to heparin administration is challenging. The regimens used as alternatives, for example anticoagulation-free dialysis, regional heparinization with protamine, direct thrombin inhibitors, prostacyclin or RCA, encounter considerable limitations. Current guidelines state that in patients with increased bleeding risks, strategies that can induce systemic anticoagulation should be avoided. Treatment strategies that avoid this include no use of anticoagulants with regular flushing or RCA [3]. To date, the use of RCA is restricted to specialized units, since its application is cumbersome [26], because it usually requires additional pumps for citrate and calcium infusions, which are not provided by standard dialysis machines, as well as the need for careful monitoring of electrolytes. These issues not only increase the complexity of the RCA procedure but also the likelihood of complications, the most dangerous being systemic hypocalcemia, since it can cause life-threatening arrhythmias [30]. Therefore, heparin-free dialysis using saline infusion is currently *de facto* considered as the gold standard in patients with high risk of bleeding [1,2] and serves as the control intervention in the present trial. For obvious logistical and technical reasons, the study is conducted as open-label and the primary endpoint could not be assessed blindly. Indeed, neither the predilution process nor the saline flushes can be masked and the dialyzers can easily be differentiated by the nursing staff (different housings, different membrane colors and transparency), since they must be carefully examined during the dialysis treatment and they cannot be completely covered by a label aimed at preventing any differentiation between the two groups. In order to minimize potential bias due to the open-label design, it was decided to have the study primary endpoint: 1. evaluated by the most widespread semi-quantitative clotting scale used in research [13,14,19,20,25,26]; 2. independently rated by two observers; in case of discordance between the two observers or in case of premature session stoppage (grade 4), the final adjudication must be made by a third authorized and trained person (the principal investigator or registered co-investigators); and 3. training and certification of nurses and investigators with regard to grading.

Several protocols of heparin-free dialysis are currently being used in routine practice, which may include saline flushes delivered at frequent intervals, requiring close monitoring by dialysis staff, or predilution, where a continuous infusion of saline is run to the dialyzer; the former procedure being the most commonly used. Taking into account this heterogeneity and in order to increase the external validity of the study results, it was decided to allow both types of saline infusions, which reflect real-life situations; however, accompanied with guidelines relative to the volume and output of saline infusion, in order to minimize the heterogeneity within the control group. To the best of our knowledge, the HepZero study is the first international, multicenter, randomized, controlled study aimed at comparing two techniques of heparin-free dialysis, including its gold standard, in two parallel groups, in an open-label design. It is sufficiently powered to first evaluate the non-inferiority of Evodial (which may allow a decrease in dialysis staff workload during heparin-free dialysis sessions) then its potential superiority versus the standard care of saline infusions, and may therefore have major clinical implications for patient care.

## Trial status

Trial status at the time of submission the 15^th^ January 2013: 245 patients recruited.

## Abbreviations

DSMB: Data and Safety Monitoring Board; PEI: Polyethyleneimine; RCA: Regional citrate anticoagulation; UF: Ultrafiltration.
